# Designing the selenium and bladder cancer trial (SELEBLAT), a phase lll randomized chemoprevention study with selenium on recurrence of bladder cancer in Belgium

**DOI:** 10.1186/1471-2490-12-8

**Published:** 2012-03-21

**Keywords:** Selenium, Bladder cancer, Transitional Cell Carcinoma, Chemoprevention, Randomized clinical trial, Urology

## Abstract

**Background:**

In Belgium, bladder cancer is the fifth most common cancer in males (5.2%) and the sixth most frequent cause of death from cancer in males (3.8%). Previous epidemiological studies have consistently reported that selenium concentrations were inversely associated with the risk of bladder cancer. This suggests that selenium may also be suitable for chemoprevention of recurrence.

**Method:**

The SELEBLAT study opened in September 2009 and is still recruiting all patients with non-invasive transitional cell carcinoma of the bladder on TURB operation in 15 Belgian hospitals. Recruitment progress can be monitored live at http://www.seleblat.org. Patients are randomly assigned to selenium yeast (200 μg/day) supplementation for 3 years or matching placebo, in addition to standard care. The objective is to determine the effect of selenium on the recurrence of bladder cancer. Randomization is stratified by treatment centre. A computerized algorithm randomly assigns the patients to a treatment arm. All study personnel and participants are blinded to treatment assignment for the duration of the study.

**Design:**

The SELEnium and BLAdder cancer Trial (SELEBLAT) is a phase III randomized, placebo-controlled, academic, double-blind superior trial.

**Discussion:**

This is the first report on a selenium randomized trial in bladder cancer patients.

**Trial registration:**

ClinicalTrials.gov identifier: NCT00729287

## Introduction

In Belgium, 2159 patients were newly diagnosed with a primary bladder cancer in 2008. These numbers have been stable over the last five years. The incidence and mortality rates increase sharply with age and about two-thirds of patients are ≥ 65 years old. The mean age of diagnosis is 73 years for men and 74 years for women. In the age group 45-59 years, the male/female ratio is 3:3, while in the age group 60-74 years the incidence rates in males are more than fivefold than the rates in females. The relative 5-year survival is 47% for men and 54% for women [1]. Almost 400,000 bladder cancer cases occurred worldwide in 2008 [2]. Moreover, in the USA and probably in most Western countries, bladder cancer is the most expensive cancer in terms of healthcare expenditure [3] because of lifetime ongoing cystoscopies. Any reduction in the need for cystoscopies reduces the cost and even more important, improves quality of life.

Evidence supporting the use of selenium as a general cancer preventive agent includes proof from geographical, animal, in vitro, epidemiological and intervention studies. High selenium intake in Venezuela is associated with a reduced cancer risk [4]. In animal models, antitumourigenic activity has been observed for metabolites of naturally occurring forms of selenium such as selenomethionine, selenocysteine and methylselenocysteine and inorganic selenium salts, such as selenite and selenate [5,6]. Recent in vitro studies have demonstrated that selenium may be an effective chemopreventive and anticancer agent with a broad spectrum against several human cancer cells (prostate, colon, bladder, lung, liver, ovarian, leukemia). In total, twenty-eight different selenium compounds have been reported to have anticancer, chemopreventive or apoptotic activities [7-9]. Three case-control studies reported an increased risk of bladder cancer, associated with lower serum [10] and toenail [10-12] selenium concentrations. A meta-analysis of bladder cancer incidence in five observational studies [13-17] found an inverse association with an overall risk estimate of 0.67 (95% CI 0.46 to 0.97) suggesting a protective effect of higher selenium levels against bladder cancer [18]. The Nutritional Prevention of Cancer (NPC) study from Clark in 1996 was the first intervention study that showed a decrease in the incidence of prostate, lung and colorectal cancers in the selenium-supplemented group of older Americans. The effect seemed to be the strongest in the individuals with the lowest selenium status (< 123.2 ng/mL) [19,20]. Nevertheless, not all cancer prevention trials indicated reduced cancer risk by selenium supplementation. The selenium and Vitamin E Cancer Prevention Trial (SELECT) failed to show a benefit of selenium supplementation in reducing the risk of prostate cancer in a population of healthy men [21]. The lack of positive effect of selenium supplementation on the prostate cancer incidence observed in this study may have been due to the different form of selenium used, selenomethionine, compared to Se-enriched yeast in the NPC study [8,22].

The review of Brinkman et al. [23] and the later studies of Grossman et al. [24], Altwein et al. [25], Busby et al. [26] and Amaral et al. [27] suggest that selenium may be suitable for chemoprevention as well as for treatment. It is useful to perform a selenium trial in a country such as Belgium where the selenium intake is low due to low soil selenium content. In the Belgian case control study the mean blood selenium level in the cases was 78.77 ng/mL compared with 92.31 ng/mL in the controls [10]. This contrasts with the patients enrolled in the NPC and the SELECT trials who had higher initial plasma levels of selenium (113 ng/mL and 135 ng/mL, respectively) [28] and an intake of approximately 90 μg/day. As selenium is mainly excreted in the urine, it comes into direct contact and has prolonged exposure with the bladder mucosa, making the role as a potential chemoprevention agent biologically plausible, unlike the case in prostate cancer.

The objective of SELEBLAT is to investigate whether 200 μg/day Selenium-yeast, in addition to standard care, reduces the risk of recurrence for patients with non-invasive bladder cancer.

## Methods

### Clinical design

SELEBLAT is a phase III randomized, double-blind, placebo-controlled, multicentre, academic trial with 200 μg/day Selenium-yeast supplementation during 3 years with a subsequent follow-up period of 3 years aimed at the prevention of recurrence of non-muscle-invasive bladder cancer (NMIBC). SELEBLAT was initiated by the Department of General Practice of the University of Leuven and the Department of Urology of the University hospitals of Leuven, Belgium with funding by the Agency for Innovation by Science and Technology Belgium (IWT).

#### Outcome

The primary endpoint of SELEBLAT is the recurrence-free interval defined as the time from the date of trial entry to the date of recurrence in patients with superficial transitional cell carcinoma of the bladder. A recurrence is defined as the new occurrence of a bladder cancer at the same or at a different site as the index cancer and excluding tumours identified at the first cystoscopy at three month. Tumours identified within the first three months are considered as incompletely resected primary tumours in patients who were macroscopically tumour-free after the first resection.

A secondary endpoint is the progression-free interval defined as the time from the date of trial entry to the date of progression. Progression is defined as a recurrence with an increase in tumour grade from low grade (G1-G2) to high grade (G3), or an increase in TNM stage, or a new occurrence of carcinoma in situ (CIS) in the bladder previously free from such lesions, or a new occurrence of multiple tumours following resection of a solitary tumour, or the need for a cystectomy because of refractory disease.

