#### Statistical analysis

Final statistical analysis is on an intention-to-treat basis. Kaplan-Meier estimates of a recurrence-free interval are used to compare treatment groups descriptively, whilst log-rank tests are used to test the hypothesis of no difference between treatments. Cox proportional hazards regression models are used to estimate the Hazard risks and 95% confidence intervals comparing patients randomized to active selenium versus placebo with and without adjustment for age, sex and stage at time of diagnosis. A per protocol analysis will be performed as a sensitivity analysis. We will also test for interactions with possible additional effect modifiers such as smoking, selenium at baseline as an indicator of selenium intake. For secondary outcome measures, treatment arms are compared in terms of progression-free interval using Kaplan-Meier and log-rank tests. The reasons for excluding patients from the analysis are clearly reported.

All analyzes are performed using STATA (StataCorp. 2009. *Stata Statistical Software: Release 11*. College Station, TX: StataCorp LP)

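### The secondary progression composite counts multifocal recurrence after a solitary tumour alongside grade, stage, CIS and cystectomy events, so a reduction in recurrence alone could be reported as delayed progression

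*Protocol article*

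**What the plan says.** In the protocol article, Methods, Outcome, the secondary endpoint is the time from trial entry to progression. The definition opens with the grade route: "Progression is defined as a recurrence with an increase in tumour grade from low grade (G1-G2) to high grade (G3"). Four alternatives follow, each joined by *or*:

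- stage: "or an increase in TNM stage"
- CIS: "a new occurrence of carcinoma in situ (CIS) in the bladder previously free from such lesions"
- multiplicity: "a new occurrence of multiple tumours following resection of a solitary tumour"
- cystectomy: "the need for a cystectomy because of refractory disease"

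The same section defines the primary event broadly: "A recurrence is defined as the new occurrence of a bladder cancer at the same or at a different site as the index cancer". It leaves out tumours found up to the first cystoscopy at three months.

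Under Statistical analysis, for the secondary outcome, "treatment arms are compared in terms of progression-free interval using Kaplan-Meier and log-rank tests". Entry is limited to pTa, pT1 or CIS (Eligibility criteria). The Discussion adds that clinical recurrences count as events because many are treated by cautery with no tissue taken.

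**The concern.** Four of the five routes describe a change in the character of the disease, or its failure to respond to treatment. The multiplicity route does not. A patient with a solitary pTa G1 tumour who later has two pTa G1 tumours has progressed by definition, with grade, stage and CIS status unchanged. That patient has also had a recurrence.

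The routes open to a patient also depend on baseline status. A G3 index tumour closes the grade route, existing CIS closes the CIS route, and multiple index tumours close the multiplicity route.

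What is at stake is the meaning of a positive secondary result. A treatment that lowers the rate of new tumours also lowers the number of multifocal ones. One log-rank test on the composite could then be read as delayed progression when nothing has changed in stage, grade, CIS or cystectomy. In the other direction, an effect confined to stage or cystectomy could be diluted by multifocal events of unchanged grade and stage.

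**Working it through.** The plan gives no event rate or power for progression, so there is no figure of its own to reproduce. Three checks follow.

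**1. Who is open to which route (Table 1, first 100 patients).** Row totals in the table differ from 100, so these shares are approximate.

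- Solitary: 59/(59+36+4) = 59/99 = 59.6%; among known, 59/95 = 62%. Open to multiplicity.
- Multiple: 36/99 = 36.4%; among known, 36/95 = 38%. Closed to multiplicity.
- G3: 33/(31+35+33+4) = 33/103 = 32.0%; among known, 33/99 = 33%. Closed to the grade route.
- CIS by stage: 5/103 = 4.9%. Closed to the CIS route.
- Stage increase: open to all, since everyone enters below pT2. Cystectomy: open to all.

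A patient with a solitary G1-G2 tumour and no CIS has five routes. A patient with multiple tumours, G3 and CIS has two.

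**2. Overlap with the primary endpoint.** New multiple tumours after resection are new bladder cancers at the same or another site. Apart from the three-month exclusion, every multiplicity event is therefore also a recurrence. The reverse is not true: a solitary recurrence of unchanged grade and stage is a primary event only.

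**3. How large the multiplicity share could be.** The rates here are assumptions, because the document has none. Per recurrence: multifocal m = 0.10 to 0.50 (if solitary at baseline), grade rise g = 0.05 to 0.20 (if G1-G2), stage rise s = 0.05 to 0.15, new CIS c = 0.03 to 0.10 (if no CIS). Components are taken as independent and cystectomy is ignored. Baseline shares are solitary 59/99 = 0.596, G1-G2 66/103 = 0.641, no CIS 98/103 = 0.951.

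Progression without multiplicity, per recurrence: A = 1 − (1 − s)(1 − 0.641g)(1 − 0.951c)

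Progression with multiplicity: B = 1 − (1 − A)(1 − 0.596m)

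Share of progression qualifying by multiplicity alone: 1 − A/B

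- Other rates low (g = 0.05, s = 0.05, c = 0.03): A = 0.107. With m = 0.10, B = 0.160 and the share is 33%. With m = 0.50, B = 0.373 and the share is 71%.
- Other rates high (g = 0.20, s = 0.15, c = 0.10): A = 0.329. With m = 0.10, B = 0.369 and the share is 11%. With m = 0.50, B = 0.529 and the share is 38%.

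So 16% to 53% of recurrences would count as progression with the multiplicity route, and 11% to 33% without it. Multiplicity-only events would be 11% to 71% of progression events, which may be a minority or a majority.

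By profile, at equal component rates, the probability that a recurrence counts as progression is:

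- five routes open: 1 − 0.95 × 0.95 × 0.97 × 0.90 = 0.21, up to 1 − 0.85 × 0.80 × 0.90 × 0.50 = 0.69
- only stage and cystectomy open: 0.05 to 0.15

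The gap would narrow or reverse if stage increase or cystectomy were more frequent in high-risk patients. The document gives nothing on that.

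**The case against.** The definition is explicit and applies equally to both blinded arms, so it does not bias the treatment comparison. It concerns a secondary endpoint; the sample size and interim rules rest on recurrence. Whether multifocality belongs in progression is a definitional choice. The primary endpoint records time to any recurrence and says nothing about number, so multiplicity adds some information. Component reporting is often left to an analysis plan that is not shown here. All of this stands, and it limits the point to interpretation.

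Deleting the clause would not fully separate the two endpoints. A grade rise or new CIS still needs a new tumour, so a treatment that only reduced recurrence would still tend to reduce progression. Deletion would also make the endpoint lean more on histology, which is missing where no biopsy is taken, and it would redefine an outcome in an ongoing trial whose results are to be pooled with a similar UK trial. These are good reasons to add an analysis rather than replace the composite.

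A reader might infer more than the text supports:

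- *That the endpoint mainly repeats recurrence, or that multifocal events swamp the rest.* Both need component rates, which are absent; the assumed ranges fall on either side of one half.
- *That high-risk patients meet a ceiling.* Only single components are closed to them; stage increase and cystectomy are not.
- *That events are concentrated in the lowest-risk patients.* Those patients have more open routes, but this does not establish more events. Solitary is also not the same as low-risk: a solitary pT1 G3 patient is open to multiplicity, and Table 1 has no cross-tabulation.

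**Conclusion.** The point holds as a matter of interpretation. The composite mixes a pattern of recurrence with worsening of the disease, and the components a patient can have depend on baseline status. About 60% of patients are open to the multiplicity route and about a third are closed to the grade route. A result reported as delayed progression could rest on multifocal recurrences of unchanged grade and stage. How many such events there would be cannot be determined from the document; 11% to 71% of progression events is an illustration under assumed rates, independence and no cystectomy events. Type I error and the comparison between arms are unaffected. Because the remedy is cheap and decides what the trial can say about progression, it should be adopted.

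**What to change.** Keep the present composite. Before unblinding, prespecify beside it:

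1. A log-rank and Cox analysis of progression that omits events qualifying only by multiplicity. Its events are stage increase, G1-G2 to G3, new CIS, or cystectomy for refractory disease.
2. The number of patients with each component, by arm.
3. Stage increase or cystectomy shown separately. This is the only component set open to every patient.
4. A rule that an effect on progression is claimed only if the analysis without multiplicity supports it.
5. The number of recurrences treated without biopsy, by arm, since grade and stage will be missing for them.

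The cost is wording and a few extra tables. Histopathology and outcomes are already taken from the medical records (Data collection), and keeping the composite leaves the planned pooling as it is. The price is fewer events and a wider interval in the added analysis, plus incomplete grade and stage where no tissue was taken. The added analysis also keeps some link with recurrence through grade rise and new CIS, which is why item 3 is needed.

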#### Eligibility criteria for participants

Men and women, at least 18 years of age, who give informed consent, are eligible for inclusion in SELEBLAT, if they have undergone a transurethral resection (TUR) of a histologically confirmed transitional cell carcinoma of the bladder, stage pTa, pT1 or Carcinoma in situ (Cis). Primary and second primary tumours are included. Eligibility and exclusion criteria are:

• Men and women, aged above 18 years

• Histologically confirmed non-muscle-invasive transitional cell carcinoma (< pT2): stage pTa, pT1 or Carcinoma in situ (Cis)

• Primary and second primary tumours

• Able to be randomized within three months after transurethral resection of the bladder tumour

• Must be able to swallow pills

• Must agree not to take supplements containing selenium, apart from the trial medication

• Fertile female patients must use effective contraception

• No invasive or metastatic disease (stage pT2 or above)

• No history of any type of malignancy within the past five years

• No other serious medical or psychiatric illness that would preclude giving informed consent

• No known hypersensitivity or adverse reactions to selenium

• Not taking more than 50 mg selenium/day as a dietary supplement, including multivitamin supplements within the last 30 days

• Not concurrently participating or having participated in any other clinical trial involving a medical, surgical, nutritional or life-style intervention (unless no longer receiving the intervention and being in the follow-up phase)

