#### Investigational medicinal product (IMP)

The active product is selenium (200 μg/day, in the form of high-selenium yeast, SelenoPrecise from PharmaNord, Vojens, Denmark). A six-month intake of 200 μg of SelenoPrecise yeast increases the plasma selenium levels on average from a baseline value of (mean ± SD) 92 ± 20 ng/mL to 196 ± 42 ng/mL. The increase of the plasma selenium level is dose-dependent [29]. Patients in each study arm received an oral tablet (selenium or placebo) to be taken daily, in addition to standard care. Standard care is provided as described by Oosterlinck in the "Guidelines on diagnosis and treatment of superficial bladder cancer" [30]. Placebos have been manufactured to be identical in appearance, smell and taste to the active agents. They were identical in their composition except for the active agents. The duration of the treatment in both arms is three years, in absence of concurrent illness that prevents further administration of treatment, an unacceptable adverse event, an unacceptable toxicity or if a patient decides to withdraw from the study. Treatment stops if general or specific changes in the patient's condition render the patient ineligible for further treatment in the judgment of the investigator or the treating physician.

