#### Safety and toxicity

Data on toxicity of selenium yeast are available from two animal studies while a number of human intervention studies show that the chronic administration of Se-yeast up to 800 μg/d provides no evidence of toxicity [19].

In 2008 there was an outbreak of selenium toxicity (selenosis). The source was identified as a liquid dietary supplement that contained 200 times the labelled concentration of selenium in the form of sodium selenite. Of 201 cases identified in ten states in the US, one person was hospitalized. The median estimated dose of selenium consumed was 41749 μg/day. Frequently reported symptoms included diarrhoea (78%), fatigue (75%), hair loss (72%), joint pain (70%), nail discoloration or brittleness (61%), and nausea (58%) [32]. It is suggested that hair, fingernails and toenails may all act as excretory organs when excess amounts of selenium are ingested [33]. The Food and Nutrition Board-Institute of Medicine [34] fixed the highest daily level of selenium that is likely to pose no risk of adverse health effects in almost all individuals at 400 μg selenium per day [31].

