Selenized yeast was selected for use in this trial because of its availability and well-characterized safety profile. In both the SELECT trial (prostate cancer prevention) and the NPC trial (basal cell or squamous cell skin cancer prevention), selenium supplementation was not significantly associated with any of the cardiovascular disease endpoints during 7.6 years of follow-up (all cardiovascular diseases, myocardial infarction, stroke, all cardiovascular disease mortality) [48]. In secondary analyses of data from the NPC study, 58 subjects in the selenium-supplemented group (n = 600) and 39 subjects in the placebo group (n = 602) developed type 2 diabetes (hazard ratio 1.55; 95% CI, 1.03-2.33) [49]. In the SELECT trial a statistically non-significant increased risk of type 2 diabetes was observed in the selenium group (RR, 1.07; 99% CI, 0.94-1.22) but not in the selenium vitamin E group [21]. A secondary analysis was carried out using data from a pre-existing randomized clinical trial designed to investigate the effects of selenium yeast on prostate cancer progression (Watchful Waiting Trial) [50]. There were no statistically significant differences in glucose levels during the course of the trial in men supplemented with selenium as compared with those on placebo. Laclaustra et al. reports that in U.S. adults, high serum selenium concentrations were associated with higher prevalence of diabetes and higher fasting plasma glucose and glycosylated hemoglobin levels. Mean serum selenium level in this trial was 137.1 ng/mL [51]. In the New England case-control study, independently of the selenium serum level, an increase bladder cancer risk was associated with a history of diabetes (adjusted odds ratio = 2.2, 95% CI, 1.3 to 3.8). The risk may be greater among patients taking oral hypoglycemics and those with diabetes of longer duration [52]. Total cholesterol, triglycerides, LDL cholesterol, and fasting serum glucose concentrations significantly increased with serum selenium concentration in the Taiwanese elderly. The mean serum selenium concentration was 89.76 ng/mL [53]. In the UK, the PRECISE Pilot trial randomized 501 elderly volunteers of relatively low selenium status [mean (SD) plasma selenium 88.8 (19.2 ng/mL)] to a six-month treatment with 100, 200 or 300 mg selenium/day as high-selenium yeast or placebo yeast [36]. Supplementation at 100 and 200 mg selenium/day lowered total serum cholesterol and non-HDL cholesterol [54]. The effects of a long-term selenium supplement on blood pressure are inconsistent. Laclaustra et al. reported that blood pressure increases if the plasma selenium level is higher than 160 ng/mL [55]. In a cross-sectional study with selenium in Belgium, the Flemish Study on Environment Genes and Health Outcomes (FLEMENGHO), 20 ng/mL higher plasma selenium level was associated with a clinically not relevant lower blood pressure with an effect sizes of 2.2 mmHg systolic (95% CI -0.57 to -5.05; p = 0.009) and 1.5 mmHg diastolic (95% CI -0.56 to -2.44; p = 0.017) in men, but not in women [56]. As in Belgium the daily intake of selenium is low, we think that patients taking selenium for three years can only benefit from this treatment, including of blood pressure reduction.

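### The limit on prior selenium supplements is printed as 50 mg/day, 250 times the trial dose, so as written it restricts practically no ordinary supplement user

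*Protocol article*

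**What the plan says.** Under Eligibility criteria for participants, the Protocol article gives one rule on selenium taken before entry: "Not taking more than 50 mg selenium/day as a dietary supplement, including multivitamin supplements within the last 30 days". A separate item in the same list requires patients to agree to take no selenium-containing supplement other than the trial product.

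The other selenium amounts that bear on this trial are in micrograms:

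- Investigational medicinal product: "The active product is selenium (200 μg/day, in the form of high-selenium yeast".
- Safety and toxicity, on the reference level set by a national nutrition board: "likely to pose no risk of adverse health effects in almost all individuals at 400 μg selenium per day".
- Safety and toxicity, on the outbreak: "The median estimated dose of selenium consumed was 41749 μg/day".
- Drug interactions/precautions links adverse symptoms to intakes above 700 μg a day. Safety and toxicity reports no evidence of toxicity for selenium yeast up to 800 μg a day.

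Milligrams appear for selenium in one other place. The Discussion describes another trial of selenium yeast, with the sentence beginning "Supplementation at 100 and 200 mg selenium/day lowered total serum cholesterol".

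**The concern.** An upper limit on prior intake should separate patients who enter with selenium already raised by supplements from those who do not. A limit far above every other dose in the document cannot do that.

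This matters for the treatment contrast. The case for running the trial in Belgium rests on low selenium intake. The sample-size section bases the expected effect on a rise in plasma selenium of about 100 ng/mL. The introduction reports that an earlier intervention trial seemed to have its strongest effect in people with the lowest selenium status. A patient whose level is already raised at entry has less of that rise to gain on active treatment. On placebo, such a patient starts above the level assumed for an unsupplemented control.

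**Working it through.** **1. The plan's own figure.** The limit is stated without a derivation, so there is nothing to reproduce. The check is a unit conversion and a comparison with the article's other figures.

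50 mg/day × 1,000 μg/mg = 50,000 μg/day

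**2. Ratio of the limit to each comparator** (50,000 ÷ comparator)

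| Comparator | Section | μg/day | Ratio |
|---|---|---|---|
| Trial dose | Investigational medicinal product | 200 | 250 |
| Cited no-risk level | Safety and toxicity | 400 | 125 |
| Intake above which symptoms are reported | Drug interactions/precautions | 700 | 71.4 |
| Highest selenium-yeast dose cited without toxicity | Safety and toxicity | 800 | 62.5 |
| Outbreak median | Safety and toxicity | 41,749 | 1.20 |

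**3. Is the outbreak figure itself in the right unit?** The article attributes the outbreak to "a liquid dietary supplement that contained 200 times the labelled concentration of selenium in the form of sodium selenite". If people took roughly the labelled amount (an assumption), the labelled dose would be 41,749 ÷ 200 = 209 μg/day. That is of the same order as the trial dose, so micrograms is credible for the comparator.

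**4. What the literal limit lets in.** The product section says that six months on 200 μg/day raises mean plasma selenium from 92 to 196 ng/mL, a rise of 104 ng/mL. A person who took that amount up to entry is at 200 ÷ 50,000 = 0.4% of the limit and is eligible. Such a person could start near the level that the active arm is meant to reach.

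**5. How common could this be?** Baseline plasma selenium in the first 100 patients has mean 84.8 and SD 18.5 ng/mL (Baseline characteristics).

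- The mean lies between those of the Belgian cases (78.77) and controls (92.31) quoted in the introduction.
- The low-status cut quoted there is 123.2 ng/mL, which is (123.2 − 84.8) ÷ 18.5 = 2.1 SD above the trial mean.
- The level of 196 ng/mL is 196 − 84.8 = 111.2 ng/mL above the mean, or 6.0 SD.
- By the one-sided Chebyshev (Cantelli) bound, the share at or above 196 ng/mL cannot exceed SD² ÷ (SD² + distance²) = 342.25 ÷ (342.25 + 12,365.44) = 0.027. That is at most 2 of 100, whatever the shape of the distribution.

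The last line assumes that all 100 patients had a measurement. It does not count users with smaller rises.

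**The case against.** The strongest reply accepts the wrong unit but holds that little follows from it.

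- **Continued double intake.** A reader might infer that patients may add the trial product to their own supplements, which would be a direct safety problem. The article does not support this: the list requires them to agree to take no other selenium supplement. Only carry-over remains. This part of the reply stands.
- **The effect-modifier analysis.** A reader might infer that the planned interaction with baseline selenium is spoiled. Baseline blood is taken from all patients for selenium measurement, so a recent user is recorded with the raised value. That value may fall after the user stops, which allows some misclassification, but it arises before randomization and does not depend on arm. This also stands.
- **Frequency.** The early baseline data do not point to many heavy users. This stands for the first 100 patients only; 177 had been recruited at the time of writing.
- **A slip in the article only.** The milligram unit recurs in the Discussion for an outside trial, which fits a writing or typesetting slip. A symbol lost when the text was read from PDF cannot be ruled out either, although the microgram sign is printed correctly in many other places. The full protocol and site documents are not shown, so it cannot be claimed that sites applied 50 mg.
- **An analysis already planned.** The Discussion promises an analysis of additional selenium from food supplements, so a further sensitivity run is not essential.

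None of this makes the criterion right as printed. The rule on supplements during the trial does not replace a limit on the 30 days before it.

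**Conclusion.** The point holds as an error in a stated eligibility threshold. The printed limit is 250 times the trial dose, 125 times the cited no-risk level and 1.2 times the outbreak median. Taken literally, it would exclude practically no ordinary supplement user and so does not limit intake before entry.

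It is tempting to say that it excludes nobody at all. That is not proven: 41,749 μg/day is a median, and some people in the outbreak may have taken more than 50,000 μg/day.

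The consequence is carry-over in individual patients, which may narrow their selenium contrast. Because eligibility is settled before randomization, this would tend to dilute a treatment difference and would not favour one arm. The baseline data suggest that it is not widespread, though a mean and SD cannot exclude individual cases. These conclusions assume that the printed text is what the authors wrote. They make no claim about which limit sites used.

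**What to change.** 1. Reconcile the eligibility list with the Investigational medicinal product and Safety and toxicity sections. The sponsor should confirm the intended limit and its unit and correct the criterion. No value is proposed here.
2. Check whether the full protocol, case report form and site checklists carry the same figure, and correct them if they do. Check the milligram doses given for the other trial in the Discussion as a likely recurrence of the slip.
3. Compare the supplement use in the baseline questionnaire and the baseline selenium of enrolled patients with the confirmed limit, and report how many exceed it.
4. Optionally, add to the planned analysis of supplement intake one run that leaves out anyone above the limit.

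The cost is a one-line correction, a document check and a review of data already collected. The optional run adds one further analysis.
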